## 4 TRIAL DESIGN

[figure not shown]

This study is a pilot feasibility and acceptability, non-blinded, randomised control trial (RCT). It is a pilot study because it is the first of its kind to assess a generic P-PROM intervention in routine clinical outpatient care in Australia across a range of clinical contexts and using a generic PROM called the EQ-5D-Y-5L. Hence it is essential to first conduct this pilot study to ensure the intervention is feasible, acceptable and demonstrates some effectiveness in routine clinical care before conducting a full-scale RCT.

A parallel group RCT methodology with an intervention and control arm will be utilised. Participants (children) will be randomly allocated to the intervention and control arm at a 1:1 ratio. An RCT methodology is being employed as it is the gold standard method for assessing the effectiveness of an intervention on an outcome.[9] RCT's balance participant characteristics (both observed and unobserved) between the two study arms, allowing attribution of any differences in outcome to the study intervention, which is not possible with any other study design.[9] An Intention-to-treat (ITT) analysis will be utilised, whereby all participants who are randomized are included in the statistical analysis and analysed according to the group they were originally assigned, regardless of what intervention (if any) they received.

Participants allocated to the intervention arm will receive the study intervention (see details below). Participants allocated to the control arm will receive standard care from their treating clinician at The Royal Children's Hospital at their outpatient clinic appointment.

The trial will run for a 5-10 week period in each outpatient clinic. The exact dates of the trial may differ between outpatient clinics, however, the trial will be run for 5-10 weeks in all outpatient clinics. The trial period is likely to be at a similar time (early 2024), however, the exact start date of the trial period may differ clinic to clinic and will be decided based on what is most appropriate for each outpatient clinic. During this 5-10 week period, all participants will have at least one scheduled outpatient clinic appointment with a participating outpatient clinic at The Royal Children's Hospital. All participants will also be asked to complete a baseline survey before their outpatient clinic appointment. It is expected that participants will only have one outpatient clinic appointment during this trial period.

This pilot RCT will be a single site study, conducted at RCH in Melbourne Australia. The study will be conducted in the following outpatient clinics at this site: complex care asthma clinic, centre for

---

community child health sleep clinic, centre for community child health encopresis clinic, and colorectal pelvic reconstruction service chronic constipation clinic. Supporting department declarations have been obtained for each department.

## **5 TRIAL POPULATION**

Children aged 4-17 years (inclusive) of age at the time of randomisation, their primary caregiver(s), and clinicians who attend or service the following outpatient clinics at The Royal Children's Hospital during the 5-10 week trial period will form the trial population: complex care asthma clinic, centre for community child health sleep clinic, centre for community child health encopresis clinic, and colorectal pelvic reconstruction service chronic constipation clinic.

The child aged range that informs the trial population is based on the validated age range of the generic P-PROM which forms part of the intervention, the EQ-5D-Y-5L. The EQ-5D-Y-5L is scientifically validated for use in children aged 4-17 years.[10]

Both the 1) patients who attend a participating outpatient clinic as well as 2) the clinicians who service a participating outpatient clinic during the trial period are considered participants in the trial. The patients (children) who attend a participating outpatient clinic will be randomised. Outcomes will be collected from both patients/their caregivers as well as clinicians.

### **5.1 Inclusion criteria**

All participants must meet one of the following criteria to be enrolled in this trial:

- Is a child aged 4-17 years (inclusive) at the time of randomisation and who has an appointment (either new or review and either face to face or telehealth) with one of the participating RCH outpatient clinics during the 5-10 week trial period.
- Is a service provider (including clinicians, nurses, allied health staff) who provides outpatient care to children aged 4-17 years (inclusive) at The Royal Children's Hospital in one of the participating RCH outpatient clinics during the trial period.

All participants must meet the following criteria to be enrolled in this trial:

- Provides informed consent / or has a legally acceptable representative capable of understanding the informed consent document and providing consent on the participant's behalf.

### **5.2 Exclusion criteria**

Patients meeting any of the following criteria will be excluded from the trial:

- Children with a social flag on their electronic medical record (because they will not be able to access the RCH patient portal)
- Not able to communicate in English or require a translator as per their electronic medical record (because portal only available in English)

### **5.3 Screen failures**

Screen failures are defined as participants who consent to participate in the trial but who are found, during the screening procedures, to be ineligible to continue in the trial. They therefore do not receive the intervention / will not randomised.

---

## 5.4 Recruitment and identification of potential participants

### Child/caregiver recruitment:

Potentially eligible children will be recruited via their caregivers and will be identified by participating outpatient clinic staff. Staff from the participating RCH outpatient clinics will send the caregivers of potentially eligible patients a letter approximately 1-2 months before the beginning of the trial period notifying them about the study and that they may be contacted by a member of the research team. The letter will be signed off by the head of the relevant outpatient department (i.e., if they are a patient of the complex care asthma clinic this is who the letter will be from). The letter will provide them with an email address they can contact if they would not like to be contacted by the research team. They will be provided 2-weeks to email and decline to be contacted.

Two weeks after the letters have been sent, RCH clinic teams will provide the research team with a list of the potentially eligible patients who have not declined to be contacted by the research team. This list will include child and caregiver names, child date of birth, contact phone number, contact email address (if available), treating clinician name, upcoming appointment dates, and hospital URN. All researchers who are provided this information will also hold an honorary appointment with the relevant RCH department, ensuring they hold rightful access to this information.

The research team will then contact the potentially eligible patients/caregivers who have not declined to be contacted by the research team to explain the study and ask if they are interested in taking part in the study or finding out more. The research team may contact patients/caregivers via phone call, text, or email. The research team will contact the patient/caregiver a maximum of four times prior to their appointment at the RCH. If they have not been able to contact the patient/caregiver prior to their appointment, the research team may approach the patient/caregiver in the RCH clinic waiting room prior to their appointment. Only patients or the caregivers of patients who have not declined to be contacted by the research team will be approached.

If potentially eligible patients/caregivers demonstrate interest in taking part in the study, they will be directed to the online information, screening, and consent form.

It is estimated that across these outpatient clinics approximately 100 children will be recruited and randomised to either the intervention or control arm (i.e., approximately n=50 in each arm).

### Clinician recruitment:

A total of four outpatient clinics at RCH have agreed to take part in the pilot: complex care asthma clinic, centre for community child health sleep clinic, centre for community child health encopresis clinic, and colorectal pelvic reconstruction service constipation clinic. Participating outpatient clinics have already been established and head of department sign off has been obtained.

Potentially eligible clinicians will be invited via email to participate in a short weekly survey while the trial is running and a short follow up survey.

It is estimated that across these four outpatient clinics approximately 10 clinicians will be recruited to complete clinician surveys.

## 5.5 Consent

### Child/caregiver consent:

Prior to performing any trial-specific procedure (including screening procedures to determine eligibility), informed consent will be obtained for each participant.

---

The process will be that the investigator or delegated member of the trial team will discuss the trial with relevant family members: parent/legal guardian and where appropriate the child/adolescent participant. Age-appropriate information will be provided to the child/adolescent in accordance with their level of maturity where required.

The investigator will provide the Participant Information and Consent Form to the parent/legal guardian and, where appropriate, to the child/adolescent. This will describe the purpose of the trial, the procedures to be followed, and the risks and benefits of participation.

The Participant Information and Consent Form will be provided online via REDCap. The parent/guardian or child will be able to contact the Principal Investigator via phone or email to ask any questions about the trial. The investigator will answer any questions about the trial.

The parent/legal guardian will be invited to provide online written consent. Where deemed competent and mature to provide consent, the child/adolescent will also be invited to also provide written online consent. As the level of maturity is not able to be determined by the Investigator prior to the trial as most contact will be via phone or email, adolescents will not be able to consent without first having obtained consent from their parent/legal guardian. Consent will be voluntary and free from coercion.

It will be documented in the participant's REDCap record and EPIC record that consent has been provided. When all the inclusion/exclusion criteria have been addressed and the eligibility of the participant confirmed, the participant may be assigned to a trial arm/intervention. Any participant determined to be ineligible will be captured online via REDCap alongside the reason for ineligibility.

#### **Clinician consent:**

Clinician consent to take part in surveys and qualitative focus groups will be implied (i.e., if the clinician reads the invitation email and then completes the online survey or takes part in the focus group, their consent will be implied). It is not felt necessary to ask for explicit written consent from clinicians given their familiarity with the pilot trial and as they will have the opportunity not to complete the surveys or take part in the focus group if they do not wish to. Furthermore, a key finding from the co-design phase of this study (*RCH HREC #92769, titled 'Co-designing a generic Paediatric Patient Reported Outcome Measure (P-PROM) intervention for use in Routine Outpatient Care for Kids (ROCK)'*) was that we needed to make all data collection from clinicians as quick and simple as possible, implied consent was one way to achieve this.

## **6 INTERVENTION**

### **6.1 Intervention arm**

Participants in the intervention arm will be asked to complete a generic P-PROM, specifically the EQ-5D-Y-5L, and the results of this generic P-PROM will be displayed back to the family (child and caregiver) and clinician.

### **6.2 Intervention**

The intervention has been co-designed with key stakeholders, including clinicians, caregivers, and patients. See appendices for full description of intervention.

**The patient/their caregiver will be asked to complete a generic P-PROM, specifically the EQ-5D-Y-5L prior to attending their outpatient clinic appointment.** In addition to completing the EQ-5D-Y-5L, the patient/their caregiver will be asked to specify which, if any, of the areas covered in the questionnaire

---

they would like to discuss in their upcoming appointment. If they tick that they would like to discuss any of these areas in their upcoming appointment, this will flag as an important result (highlighted in red and bold) when the results are displayed back to the clinician. The patient/ their caregiver will be asked to complete the EQ-5D-Y-5L and this additional question 7-days before their appointment at the Hospital. They will be asked to do this via The Royal Children's Hospital patient portal system. If they do not already have the patient portal set up, the research study team will help them set this up. The patient portal is connected to the child's electronic medical record and hence their responses to the generic P-PROM and additional question will be visible to the staff at The Royal Children's Hospital who have access to that child's records. If participants are not able to sign up to the RCH patient portal, a researcher will provide them with a paper copy to be completed in the waiting room on the day of their appointment. The paper copy can then be provided to the clinician in the appointment. If the child is aged eight years or older and able to answer questions about their health or wellbeing (established during baseline survey), we will ask the child to complete the generic P-PROM (i.e., child self-report). If the child is seven years or younger or not able to answer questions about their health or wellbeing, we will ask the child's caregiver to complete the generic P-PROM (i.e., parent proxy report). The age ranges child self-report/parent proxy report is based on age ranges the generic P-PROM, EQ-5D-Y-5L, has been validated in and is the age range suggested by the instrument developer.[10]

**The results of the generic P-PROM will be displayed to patients/ their caregivers and clinicians.** If completed via the RCH patient portal, children and their caregivers will be able to view a summary of their generic P-PROM results via the portal and clinicians will be able to view a summary of their generic P-PROM results via the child's electronic medical record. In the summary of results displayed to clinicians, if the child or their caregiver have indicated they would like to discuss any of the health areas covered in the generic P-PROM with their clinician in the next appointment, this will be flagged and highlighted in red and bold so that this visually alerts the clinician (see Figure 1a). If completed on paper, the patient or caregiver will hand a physical copy of the completed generic P-PROM to the clinician. If the child or their caregiver have indicated they would like to discuss any of the health areas covered in the generic P-PROM with their clinician in the appointment, this will be flagged as this question will be bolded with a red background to draw attention to this.

**Training will be provided to clinicians regarding how to address any health concerns that might arise from the generic P-PROM.** Prior to the trial period, all clinicians in participating outpatient clinics will be provided with a 30-minute co-designed training session on what the intervention is and how to respond to responses provided by patients on the generic P-PROM. This will include case vignette examples.

**Resources will be provided to both the child/caregiver as well as the clinician regarding what they can do to address any health concerns that might arise from the generic P-PROM.** The Clinician and Family PROM Resource and Support Tool has been designed in collaboration with clinicians who took part in the co-design phase of this project and has also been checked by any relevant RCH clinical departments. For example, the RCH social work team has reviewed and approved the places in which a referral to RCH social work has been suggested in the support tool.

Clinicians will be provided with a clinical decision support resource to help them 1) locate the generic PROM results, 2) identify if there is a health concern to address, 3) discuss the health concern with the patient to establish what supports might be needed, and 4) what supports might be appropriate. The Clinician and Family PROM Resource (Appendix M) will be introduced to clinicians as part of their 30-minute training to ensure they are familiar with the resource. Clinicians will be able to access an electronic copy of all pages of the Clinician and Family PROM Resource (Appendix M) via EPIC during the period of the trial. Additionally, a printed and laminated copy of all pages of the PROM resource

---

(with links replaced with QR codes) will be available on the wall or desk of each outpatient clinic room during the period of the trial.

Patients and their caregivers will also receive a resource regarding where they can seek support themselves if they have any concerns about any of the health areas covered by the generic P-PROM. If the generic P-PROM is completed by the parent or caregiver, they will receive pages 3 and 4 of the Clinician and Family PROM Resource and Support Tool, the 'Caregiver and Parent Resources' section. If the generic P-PROM is completed by the child, they will receive pages 5 and 6 of the Clinician and Family PROM Resource and Support Tool, the 'Resources for young people' section. If the generic P-PROM is completed online via the RCH patient portal, the resource will be available to them online in the patient portal. If they complete the generic P-PROM on paper in the waiting room, they will receive a paper copy of the resource (with links replaced with QR codes).

## **7 RANDOMISATION AND BLINDING**

Randomisation will occur after completion of the baseline survey. Randomisation will be performed by a person independent to the study. Block randomization will be employed with the goal of ensuring balance between study arms. The randomisation schedule will be created by computer-generated random numbers, before the first participant has been recruited. The schedule will be held by an independent person, and allocation will not be revealed prematurely to CI. Because of these procedures, the research team will be unable to predict which group the participant will be allocated to. Once participants have been randomly allocated to either the intervention or control arm they will be informed about this via an email from the research team. This email will also include instructions for what to expect next. The study arm a participant is allocated to will be logged in both REDCap and EPIC.

This pilot RCT will be non-blinded, meaning children/their caregiver(s), treating clinicians, and researchers (including those tasked with data collection and analysis) will be aware which study arm each participant has been allocated to. A non-blinded methodology was chosen as a placebo was not feasible or practical in this pilot trial.

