### **10.4 Methods of analysis**

As this is a pilot trial, most analyses are descriptive.

| OUTCOME                                                                                                                                                                                                                            | METHOD OF ANALYSIS                                                                                                                                                                                                                                                                                                                                                                                                               |
|------------------------------------------------------------------------------------------------------------------------------------------------------------------------------------------------------------------------------------|----------------------------------------------------------------------------------------------------------------------------------------------------------------------------------------------------------------------------------------------------------------------------------------------------------------------------------------------------------------------------------------------------------------------------------|
| Acceptability and feasibility.                                                                                                                                                                                                     | 
Most acceptability and feasibility outcomes will be assessed using descriptive statistics.
 
For example, the proportion of patient/caregivers allocated to the intervention arm who completed the PROM will be described.
 
Some sub-group analyses maybe conducted where appropriate by PROM completion type (paper versus portal), appointment type (face to face versus telehealth), and outpatient clinic.
 |

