| Discussion of relevant quality-of-life domains in clinical encounter.                                                                                                                                                              | 
Descriptive & inferential statistics.
 
Proportion of patients/caregivers who report discussing quality of life domains that were relevant to them in their most recent clinical encounter. Responses will be compared between participants in intervention and control arm using a chi-squared test.
                                                                                                            |
| Holistic care provided in clinical encounter.                                                                                                                                                                                      | 
Descriptive & inferential statistics.
 
Proportion of patients/caregivers who report discussion of aspects of health beyond just the physical condition they were present for (such as emotional, social, school, hobbies, and spiritual wellbeing) in their most recent clinical encounter. Responses will be compared between participants in intervention and control arm using a chi-squared test.
           |
| Proportion of clinical encounters where a new health problem was detected.                                                                                                                                                         | 
Descriptive & inferential statistics.
 
Proportion of patients where a new health problem was detected in their most recent clinical encounter. Responses will be compared between participants in intervention and control arm using a chi-squared test.
                                                                                                                                                        |

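### No stratification by clinic is stated and the secondary comparisons are unadjusted for clinic, which leaves avoidable chance imbalance and lost precision across four different clinics

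*Protocol*

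**What the plan says.** Section 4 sets individual allocation: "Participants (children) will be randomly allocated to the intervention and control arm at a 1:1 ratio". Section 7 gives the method: "Block randomization will be employed with the goal of ensuring balance between study arms". It goes on: "The randomisation schedule will be created by computer-generated random numbers, before the first participant has been recruited". One schedule is described. Neither section 7 nor any other part of the protocol names a stratification factor or a block size.

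Section 5.4 expects that "approximately 100 children will be recruited and randomised to either the intervention or control arm (i.e., approximately n=50 in each arm"), and states that "A total of four outpatient clinics at RCH have agreed to take part in the pilot": complex asthma, sleep, encopresis and chronic constipation. The Background section describes these as separate patient groups, chosen to cover a range of settings.

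Section 10.4 names the test for each of the seven secondary outcomes. Five use the same sentence: "Responses will be compared between participants in intervention and control arm using a chi-squared test". These are discussion of relevant domains, holistic care, new problems detected, support received, and communication. The five PSQ items and the CHU9D change from baseline are compared by t-test. None of these tests carries a covariate. Clinic enters the analysis only as an optional sub-group in the acceptability and feasibility row: "appointment type (face to face versus telehealth), and outpatient clinic".

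**The concern.** Blocking a single list controls the overall arm totals. When several clinics draw from that list at the same time, each block mixes children from different clinics, and the split within any one clinic is left almost entirely to chance.

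That matters when clinic predicts outcome, which is plausible here. Whether a visit covered school or emotional wellbeing, turned up a new problem, led to a referral or satisfied the family depends on the condition, the clinician and the usual content of that clinic's appointments. If so, an uneven clinic mix moves the observed arm difference, and an unadjusted test leaves between-clinic variation in the error term.

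Section 10.1 intends the outcome data to inform sample sizes for later full trials. Arm differences shifted by clinic mix, and standard deviations that include between-clinic variation, would feed those calculations.

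**Working it through.** **The plan's own figure.** 100 × 1/2 = 50 per arm, which agrees with sections 5.4 and 10.1. No alpha, power, effect size or SD is stated, so there is no power figure to reproduce.

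**Inputs.** From the protocol: about 100 children, 1:1, four clinics, one blocked schedule. Assumed, because the protocol does not give them: clinic sizes, block size, clinic outcome rates, effect size, and the share of variance due to clinic.

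**1. One clinic of 25.** With 50 of 100 children allocated to each arm, the number of a clinic's 25 children in the intervention arm is hypergeometric, with SD √[25 × 0.5 × 0.5 × (75/99)] = 2.18. A split of 15:10 or worse has probability 0.36, and 16:9 or worse 0.165.

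**2. Any of four clinics.** Simulation of one unstratified list with clinics interleaved:

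| Clinic sizes | Block size | 60/40 or worse | 64/36 or worse | 70/30 or worse |
|---|---|---|---|---|
| 25/25/25/25 | 4 | 75% | 45% | 7% |
| 25/25/25/25 | 10 | 75% | 44% | 7% |
| 40/30/20/10 | 4 | 89% | 48% | 37% |
| 40/30/20/10 | 10 | 89% | 49% | 38% |

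For clinics of 25, 64/36 is 16:9. A split of 17:8 or worse occurs in about 20% of trials (blocks of 4). Block size hardly matters when clinics are interleaved.

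If clinics recruited strictly one after another, 60/40 or worse in at least one clinic would occur in 0 to 1.5% of trials with equal sizes, and in 0 to 33% with unequal sizes.

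**3. Effect on a proportion.** Assume clinic rates of 20, 30, 50 and 70%, with 25 children in each clinic.
- Mean rate: 0.425.
- Between-clinic variance: (0.225² + 0.125² + 0.075² + 0.275²)/4 = 0.0369.
- Total variance: 0.425 × 0.575 = 0.2444.
- Share due to clinic: 0.0369/0.2444 = 15%.
- SD of the arm difference from clinic mix alone: √[0.0369 × (100/99) × (1/50 + 1/50)] = 0.039, about 4 points. Simulation with blocks of 4 also gives 0.039.
- Ordinary standard error of the difference, for scale: √(2 × 0.2444/50) = 0.099, about 10 points.

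**4. Type I error and power.** Four clinics of 25, blocks of 4, standardised difference 0.5 for power, 5,000 runs per setting:

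| Variance due to clinic | Type I error, unadjusted test, no strata | Power, unadjusted, no strata | Power, adjusted, no strata | Type I error, unadjusted test, stratified list |
|---|---|---|---|---|
| 5% | 0.050 | 0.70 | 0.71 | 0.043 |
| 15% | 0.050 | 0.69 | 0.75 | 0.040 |
| 30% | 0.051 | 0.70 | 0.83 | 0.021 |

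The analytic power of a t-test with 50 per arm and a standardised difference of 0.5 is 0.705, which agrees with the unadjusted column. The last column shows that stratifying the list and keeping the unadjusted tests makes them conservative, so the two changes belong together.

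**The case against.** The strongest defence is that an unstratified randomised comparison is valid. Chance imbalance is already part of the standard error, and the simulated type I error stays near 0.05. This stands, and it limits the point to precision and balance.

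Several further limits also stand:
- Absence of stratification is read from silence; section 7 neither affirms nor excludes it.
- This is a pilot with mostly descriptive analyses, and many primary outcomes are collected in the intervention arm only. Only the secondary comparisons are affected.
- The CHU9D analysis uses change from baseline, which already removes stable clinic differences in level.
- Section 4 allows clinic dates to differ, which could reduce the imbalance, although it expects the clinics to run at a similar time.
- An analysis plan could add adjusted estimates. However, section 10.4 names its tests outright, and the schedule is drawn up before recruitment begins.

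Three stronger readings are tempting and are not supported:
- **That allocation is shown to be predictable.** Section 7 claims that "Because of these procedures, the research team will be unable to predict which group the participant will be allocated to". A reader might infer that blocking in an open trial makes this untrue. That would require a fixed block size that the team knows or can infer. The protocol states no size and does not say it is fixed; an independent person holds the schedule, and allocation follows consent and the baseline survey.
- **That the by-clinic descriptions would compare uneven arms.** Those sub-groups are optional and belong to the acceptability and feasibility outcomes, most of which have no control arm.
- **That large distortions are typical.** Suppose two clinics with rates of 60% and 20% split 16:9 in opposite directions while the rest balance at 40%. The false difference is (7 × 0.6 − 7 × 0.2)/50 = 5.6 points. Opposite splits of that size or worse arise in only about 4% of trials, and the SD of the shift under those rates is about 2.8 points.

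**Conclusion.** The point holds as a modest, inexpensive improvement that the sponsor should make. The protocol states no stratification by clinic and fixes unadjusted tests for all seven secondary between-arm outcomes, in a trial that deliberately spans four different clinics.

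Under concurrent recruitment and equal clinics of 25, a 16:9 or worse split in at least one clinic is close to an even chance, at about 45%. If clinic explains 15% of the variance, clinic mix contributes an SD of about 4 points to an arm difference whose standard error is about 10 points, and adjustment is worth about 5 points of power at a standardised difference of 0.5. The power gain ranges from about 1 to 13 points as the clinic share runs from 5% to 30%.

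These sizes rest on assumed clinic sizes, rates and recruitment order. The documents do not support a claim of bias, of inflated type I error, or of demonstrated predictability of allocation.

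**What to change.** - **Section 7:** state that allocation is stratified by clinic. The independent person prepares one permuted-block list per clinic, with block sizes that vary and are not disclosed to the research team. With blocks of at most 4, no clinic's arms can differ by more than 2 children.
- **Section 10.4:** adjust the secondary between-arm comparisons for clinic. Use a linear model for the PSQ items and CHU9D change, and a Mantel-Haenszel or standardised risk difference for the proportions, which avoids unstable logistic fits in small clinics. For the Likert communication item, a Cochran-Mantel-Haenszel test stratified by clinic would serve.
- **If the schedule is already in use:** keep it and make only the analysis change. The simulated power gain in the working comes from adjustment on an unstratified list.

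The cost is four generated lists in place of one, and one extra factor in each analysis. Arm totals may differ by a few children because blocks can end incomplete within each clinic.
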